## Abstract

**Background:**

Radiotherapy of head-and-neck cancer can be associated with significant toxicities including dermatitis and oral mucositis. Severe toxicities may require interruptions of the radiation treatment associated with impairment of the patients’ prognoses. This study will investigate whether the addition of a reminder app to standard care can reduce dermatitis and oral mucositis rates during radiotherapy in these patients.

**Methods:**

This randomized trial compares standard care supported by a reminder app (Arm A) to standard care alone (Arm B) with respect to grade ≥ 2 radiation dermatitis and oral mucositis at 60 Gy of radiotherapy, the minimum planned dose for patients receiving definitive or adjuvant radiotherapy for locally advanced head- and-neck cancer. Moreover, radiation-induced dermatitis and oral mucositis grade ≥ 3 at 60 Gy and both grade ≥ 2 and grade ≥ 3 at the end of radiation treatment (EOT) will be evaluated, as well as quality of life and pain. According to sample size calculations, 80 patients are required per arm within the full analysis set. Taking into account that 5% of patients will not qualify for full analysis set, 168 patients should be randomized. The impact of the reminder app will be considered clinically relevant, if the rates of grade ≥ 2 radiation dermatitis (primary endpoint) and oral mucositis (secondary endpoint) can be reduced by 20%.

**Discussion:**

If the addition of a reminder app to standard care will lead to a significant reduction of radiation dermatitis and oral mucositis, it could become a helpful tool for patients with head-and-neck cancer during radiotherapy.

**Trial registration:**

clinicaltrials.gov (NCT04110977). Registered on September 27, 2019. First patient is planned to be included in December 2019.

## Administrative information

Note: the numbers in curly brackets in this protocol refer to SPIRIT checklist item numbers. The order of the items has been modified to group similar items (see http://www.equator-network.org/reporting-guidelines/spirit-2013-statement-defining-standard-protocol-items-for-clinical-trials/).

## Introduction

### Background and rationale {6a}

Many patients with squamous cell carcinoma of the head and neck (SCCHN), particularly those patients with locally advanced disease, receive radiotherapy. If radiotherapy is administered as definitive treatment (i.e*.*, without preceding surgery), it is generally combined with chemotherapy [1]. In an adjuvant situation (i.e*.*,following surgery), concurrent chemotherapy will be administered if risk factors (incomplete resection and/or extracapsular [ECS] spread of lymph nodes metastases) exist.

Radiotherapy of SCCHN can be associated with significant toxicities including dermatitis and oral mucositis. Severe toxicities may require interruptions of the radiotherapy series that can impair the prognoses of these patients [2, 3]. To avoid severe (grade ≥ 3) radiation toxicities, it is important to avoid or postpone grade 2 toxicities. Grade ≥ 2 dermatitis and grade ≥ 2 mucositis rates were very high in previous studies (86–92% and 86–100%, respectively) and require improvement [4–6]. In the previous RAREST-01 trial that compared the dressing Mepitel® Film to standard skin care in patients irradiated for head-and-neck cancer, dermatitis rates were lower than expected in both groups [7, 8]. In the RAREST-01 trial, standard skin care was supposed to be performed four times daily, which required a high level of discipline from the patients. Daily reminders by medical staff members regarding the importance of skin care likely improved the patients’ compliance resulting in less radiation dermatitis. It may be questioned whether the daily reminders by staff members can be replaced by a mobile application (a reminder app).

### Objectives {7}

This study aims to show that standard skin care supported by a reminder app is superior to standard skin care alone regarding the avoidance of grade ≥ 2 dermatitis up to 60 Gy in patients irradiated for locally advanced head-and-neck cancers. The null hypothesis of equal grade ≥ 2 dermatitis rates in both groups is tested against the two-sided alternative hypothesis of different dermatitis rates.

### Trial design {8}

This is a randomized, active-controlled, parallel-group trial, which will primarily compare two treatments of radiation dermatitis in patients with head-and-neck cancer: standard care supported by a reminder app (Arm A) versus standard care alone (Arm B).

## Methods: participants, interventions and outcomes

### Study setting {9}

The study will be performed in Germany (one university hospital, one private practice) and Spain (two university hospitals). Study sites can be obtained at clinicaltrials.gov.

### Eligibility criteria {10}

Inclusion criteria
Histologically proven locally advanced SCCHNIndication for radiotherapy or radio-chemotherapyPossession of and ability to use a smartphoneAge ≥ 18 yearsWritten informed consentCapacity of the patient to contract

Exclusion criteria
Nasopharynx cancerPregnancy, lactationTreatment with epidermal growth factor receptor antibodies (given or planned)Expected noncompliance

Radiation dermatitis and oral mucositis will be assessed by two independent observers (specially trained nurses, technicians, or physicians) weekly during the period of radiotherapy, at 60 Gy and at end of treatment (EOT). If the graduation varies between the two observers, toxicities will be assessed by an additional observer. Observers are required to be very experienced in rating toxicities and will additionally undergo a particular briefing prior to the start of this study.

### Who will take informed consent? {26a}

Informed consent will be taken by specially trained physicians registered as investigators for this trial.

### Additional consent provisions for collection and use of participant data and biological specimens {26b}

Not applicable.

## Interventions

### Explanation for the choice of comparators {6b}

In a previous trial, daily reminders by medical staff members regarding the importance of skin care likely improved the patients’ compliance resulting in less radiation dermatitis [7, 8]. It may be questioned whether the daily reminders by staff members can be replaced by a mobile application (reminder app).

### Intervention description {11a}

#### Standard skin care

In both the experimental (A) and the control arm (B), standard skin care is to be performed by the patient from the beginning of radiotherapy. Standard skin care may vary at the participating centers. At the University of Lübeck, it includes fatty cream with 2–5% urea (fatty cream alone, if patients do not tolerate urea) and mometasone furoate cream. The treatment will be continued until 1 week after EOT or until a patient experiences grade ≥ 2 moist desquamation or grade ≥ 3 radiation dermatitis.

#### Standard mouth care

In both arms, standard mouth care is to be performed by the patient from the beginning of radiotherapy to prevent or at least postpone radiation-induced oral mucositis. At the University of Lübeck, it initially consists of an antibacterial mouth rinse to be used four times a day. If the patient experiences pain, lidocaine hydrochloride + plus dexpanthenole solution will be added. Alternatively, benzdyamine hydrochloride solution may be used. In case of an oral edema/swelling, hydrocortisone acetate may be used.

#### Reminder app

The patients in the experimental arm (Arm A) are supported by a reminder app (“CareReminder”), which has been developed by the professional company Nextlabel OHG from Lübeck, Germany. This app will remind the patients four times a day to perform skin and mouth care. Instructions are given how to perform it properly. The patients may postpone each required care procedure for up to 2 hours. Finally, the patients are asked to state for each procedure whether or not they performed it. To increase the patients’ motivation, they will earn points for each successfully performed procedure.

### Criteria for discontinuing or modifying allocated interventions {11b}

In case of grade ≥ 2 moist desquamation or grade ≥ 3 radiation dermatitis, each day antiseptic agents will be administered for wound cleansing followed by administration of silicon or calcium alginate bandage. This treatment will be continued until moist desquamation radiation disappears and radiation dermatitis improves to grade 2. If local anesthetics (lidocaine, benzdyamine) are not sufficient in reducing pain due to oral mucositis, systemic analgesics are given, usually metamizole and if required morphine derivatives.

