### Outcomes {12}

Primary endpoint is the rate of grade ≥ 2 radiation dermatitis Common Terminology Criteria for Adverse Events (CTCAE v5.0) at 60 Gy of radiotherapy, the minimum planned total dose for all patients receiving definitive or adjuvant radiotherapy for locally advanced head and neck cancer. In addition, the following endpoints will be evaluated:
Radiation dermatitis grade ≥ 2 at EOTRadiation dermatitis grade ≥ 3 at 60 Gy and at EOTRadiation-induced oral mucositis grade ≥ 2 at 60 Gy and at EOTRadiation-induced oral mucositis grade ≥ 3 at 60 Gy and at EOTQuality of lifePain

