## Data collection and management

### Plans for assessment and collection of outcomes {18a}

The following parameters will be recorded prior to radiotherapy: Demographics, medical history, concomitant diseases, physical examination, performance status, primary tumor site, stage and histology, upfront surgery, planned chemotherapy, status of skin and oral mucosa, pain, and quality of life.

The following parameters will be assessed throughout the course of the trial:
Radiation dermatitis: assessed by two observers weekly during radiotherapy, at 60 Gy and at EOT according to CTCAE v5.0 [9]. If graduation varies, a third observer will be involved.Oral mucositis: assessed by two observers weekly during radiotherapy, at 60 Gy and at EOT according to RTOG criteria [10–13]. If graduation varies, a third observer will be involved.Quality of life: assessed prior to radiotherapy, at 60 Gy and at EOT with European Organisation for Research and Treatment of Cancer (EORTC) Quality of Life Questionnaire (QLQ)-C30 Version 3.0 and EORTC QLQ-H&N35.Pain (within radiation fields): assessed prior to radiotherapy, weekly during radiotherapy, at 60 Gy and at EOT with a visual analog scale (from 0 = no to 10 = maximum pain).Other adverse events will be assessed on an ongoing basis according to CTCAE v5.0 [9].

The timeline of the study procedures including the assessments is given in Fig. 1.

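### The secondary grade ≥ 3 dermatitis endpoints record status at the 60 Gy and EOT visits, so a severe reaction that has improved to grade 2 by a visit is not counted there and the comparison depends on onset time

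*Protocol article*

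**What the plan says.** **Endpoint.** The Outcomes section (item 12) lists grade ≥ 3 dermatitis at two time points, 60 Gy and EOT. The abstract uses the same form: "radiation-induced dermatitis and oral mucositis grade ≥ 3 at 60 Gy". No worst-grade, cumulative or time-to-onset endpoint for grade ≥ 3 is named.

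**Wound care.** Section 11b gives the trigger: "In case of grade ≥ 2 moist desquamation or grade ≥ 3 radiation dermatitis, each day antiseptic agents will be administered". It also gives the end point of that care: "This treatment will be continued until moist desquamation radiation disappears and radiation dermatitis improves to grade 2". The rule applies in both arms.

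**Assessment.** Section 18a has dermatitis "assessed by two observers weekly during radiotherapy, at 60 Gy and at EOT according to CTCAE v5.0", with a third observer if the two disagree.

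**Rationale.** Section 6a states: "To avoid severe (grade ≥ 3) radiation toxicities, it is important to avoid or postpone grade 2 toxicities".

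**Related wording for grade ≥ 2.** The Objectives section speaks of superiority "regarding the avoidance of grade ≥ 2 dermatitis up to 60 Gy", and the Sample size section repeats this. The Outcomes section ties the primary endpoint to status *at* 60 Gy.

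**The concern.** Severe dermatitis can come and go within a course of radiotherapy, and the wound-care rule foresees a fall from grade 3 to grade 2. An endpoint that records the grade at one visit measures severe dermatitis still present then. It does not measure severe dermatitis suffered.

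Undercounting alone would weaken the comparison. The further difficulty is that the chance of being missed depends on onset time: an early reaction has longer to improve before the visit than a late one. The trial hopes to avoid *or postpone* toxicity, so onset time is something the app may change. If it does, visit status mixes two effects, fewer severe reactions and later ones, and they can pull the visit rates in opposite directions. EOT is also the end of follow-up (section 18b), so no later visit corrects the picture.

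At stake is the reading of the severe-dermatitis results, which bear on the trial's clinical rationale. The primary endpoint concerns grade ≥ 2.

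**Working it through.** **Stated figures.** The protocol gives no rate, onset time, healing time or power target for grade ≥ 3 dermatitis, so there is no figure to reproduce on this point. Its only power statement concerns grade ≥ 2: 80 per arm, 85% with standard care, a reduction of 20% (read as 20 points, to 65%), 80% power. Exact power at 80 per arm is 79.9% with Fisher's test and 84.8% with the uncorrected chi-square test. The present point leaves that calculation untouched.

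**Step 1. What is counted.** Take a patient at grade 3 at 44 Gy who is at grade 2 at 60 Gy and at EOT.

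| Rule | Grade ≥ 3 at 60 Gy | Grade ≥ 3 at EOT | Primary, grade ≥ 2 at 60 Gy |
|---|---|---|---|
| Status at the visit | no | no | event |
| Worst grade so far | event | event | event |

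A patient still at grade 3 at a visit counts under both rules.

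All inputs in steps 2 to 4 are assumptions.

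**Step 2. Equal true rates, different onset.** Let C be the share ever at grade ≥ 3, s the share of those with early onset, and r the share of early cases back at grade 2 by the visit. The visit rate is C(1 − s·r). With the same C in both arms and s = 0.5 against 0.2, the early-onset arm looks better by C × 0.3 × r:

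| C | r = 0.25 | r = 0.75 |
|---|---|---|
| 10% | 0.7 points | 2.2 points |
| 20% | 1.5 points | 4.5 points |
| 30% | 2.2 points | 6.8 points |

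With r = 0 there is no distortion.

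**Step 3. Fewer and later cases in Arm A.** Arm B: 30% ever grade ≥ 3, onset uniform over 40–60 Gy. Arm A: 20%, onset uniform over 50–70 Gy. EOT is at 70 Gy and each reaction stays at grade 3 for d Gy. A case is present at dose v if its onset lies between v − d and v. For d = 15 at EOT, onset must lie in 55–70 Gy: Arm B 0.30 × 5/20 = 7.5%, Arm A 0.20 × 15/20 = 15%. For d = 15 at 60 Gy, onset must lie in 45–60 Gy: Arm B 0.30 × 15/20 = 22.5%, Arm A 0.20 × 10/20 = 10%.

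| d | 60 Gy visit, B vs A | EOT visit, B vs A |
|---|---|---|
| 10 Gy | 15% vs 10% | 0% vs 10% |
| 15 Gy | 22.5% vs 10% | 7.5% vs 15% |
| 20 Gy | 30% vs 10% | 15% vs 20% |
| 25 Gy | 30% vs 10% | 22.5% vs 20% |
| Worst grade so far | 30% vs 10% | 30% vs 20% |

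At 60 Gy the difference shrinks for short d and never changes sign. At EOT it reverses when healing is short. Between 20 and 30 Gy, Arm A stays at 20% and Arm B is 0.30 × (d − 10)/20, so the rates are equal at d = 10 + 20 × 0.20/0.30 = 23.3 Gy. Above that the order is right again.

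**Step 4. Attenuation without an onset difference.** Suppose 30% against 12% ever reach grade ≥ 3, with 80 per arm. Exact power of the uncorrected chi-square test is 81.5%. If 30% of cases in each arm have improved by the visit, the rates are 0.7 × 30% = 21% and 0.7 × 12% = 8.4%, and power is 62.2%. If half have improved, the rates are 15% and 6%, and power is 46.5%. The protocol sets no power target for grade ≥ 3, so this shows only the direction of the loss.

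**The case against.** The case on the other side has real force.

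- **No sentence says that an improved grade ≥ 3 reaction is disregarded.** True. The rule follows from the plain sense of *at*. The *up to 60 Gy* wording in the Objectives and Sample size sections concerns grade ≥ 2 only. It shows that the counting rule is unsettled, which is a reason to state it.
- **The wound-care rule says when care stops, not that this happens before a visit.** This stands. A reader might infer that treated severe cases as a group are scored as free of severe dermatitis. The protocol does not support that: only cases already below grade 3 at the visit are missed, and only at that visit.
- **The primary endpoint.** A reader might infer that these patients drop out of it too. They do not if they are at grade 2 at 60 Gy.
- **The reversal depends on chosen inputs.** This stands. It needs healing shorter than about 23 Gy and an EOT at 70 Gy. The protocol gives 60 Gy as the minimum planned dose, and for patients planned to that dose the two visits coincide.
- **The analysis plan may settle it, and the weekly data are kept.** Partly. A derivation detail may be left to that plan, but here the protocol itself ties the endpoint to two time points. The Kaplan-Meier and log-rank methods in section 20a are generic, and no time-to-grade-3 endpoint is named.
- **Status at a fixed dose compares arms at equal exposure.** It is a legitimate quantity, and worth keeping as a description. It answers a different question from whether severe dermatitis was avoided.

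**Conclusion.** The point holds for the secondary grade ≥ 3 dermatitis endpoints. As worded, they miss severe reactions that have improved by the visit, and the share missed can differ between arms if onset times differ. The size and direction of the effect cannot be derived from the protocol. Under the assumed inputs it ranges from nothing (no recovery before the visit), through a smaller difference between arms, to a reversed order at EOT only.

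A reader might conclude that the app's severe-dermatitis result will be biased in a known direction, or that a stated power is lost. Neither is supported: every rate, onset and healing input is assumed, and grade ≥ 3 has no power target. The case for change is that the present definition is exposed to onset time in a trial that hopes to postpone toxicity, while a definition without that weakness is available from data already planned.

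**What to change.** In the Outcomes section, define each grade ≥ 3 dermatitis endpoint as the worst agreed grade at any scheduled assessment from the start of radiotherapy up to and including 60 Gy, and likewise up to and including EOT. This agrees with the *up to 60 Gy* wording of the Objectives and Sample size sections. Report status at each visit as a descriptive table. If status at the visit is what is intended, say so explicitly.

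The cost is one sentence in the endpoint definition, carried into the analysis plan. The weekly two-observer grades are already collected, so no visit is added, and clinical management is unchanged. The small downside is that cumulative rates will be higher than point-in-time rates and not directly comparable with them.

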### Strategies to improve adherence to interventions {11c}

Not applicable.

### Relevant concomitant care permitted or prohibited during the trial {11d}

 If required, any type of concomitant care and interventions are permitted during the trial for treatment of other radiotherapy- or radio-chemotherapy-related toxicities and comorbidities not related to radiotherapy or radio-chemotherapy.

### Provisions for post-trial care {30}

Following EOT (i.e., end of study), the patients receive the standard follow-up program for patients with head- and-neck cancer. Harm from trial participation is not expected, since all participating patients receive the same anticancer treatment as they would have received if not participating.

### Outcomes {12}

Primary endpoint is the rate of grade ≥ 2 radiation dermatitis Common Terminology Criteria for Adverse Events (CTCAE v5.0) at 60 Gy of radiotherapy, the minimum planned total dose for all patients receiving definitive or adjuvant radiotherapy for locally advanced head and neck cancer. In addition, the following endpoints will be evaluated:
Radiation dermatitis grade ≥ 2 at EOTRadiation dermatitis grade ≥ 3 at 60 Gy and at EOTRadiation-induced oral mucositis grade ≥ 2 at 60 Gy and at EOTRadiation-induced oral mucositis grade ≥ 3 at 60 Gy and at EOTQuality of lifePain

### Participant timeline {13}

A total of approximately four contributing centers are planning to participate, which aim to include an average of 21 patients per year. The recruitment of all 168 patients should be completed within 24 months. The treatment period will be 6–7 weeks. This equals a total running time for the trial of 26 months.

### Sample size {14}

This study aims to show that standard skin care supported by a reminder app is superior to standard skin care alone regarding the avoidance of grade ≥ 2 dermatitis up to 60 Gy in patients irradiated for locally advanced head-and-neck cancers.

The null hypothesis of equal grade ≥ 2 dermatitis rates in both groups is tested against the two-sided alternative hypothesis of unequal dermatitis rates. The calculation of the sample size considered the following assumptions:
Application of a chi-square testTwo-sided significance level of 5%Rates of grade ≥ 2 dermatitis of 86–92% with standard care alone according to previous studiesAssumption of a grade ≥ 2 dermatitis rate of 85% in the standard care alone group (“worst-case”)Clinical importance of the impact of the reminder app = reduction of grade ≥ 2 dermatitis by 20%Statistical power of 80%

When considering these assumptions, 80 patients are needed per arm within the full analysis set. Assuming that 5% of the recruited patients will not qualify for the full analysis set, 168 patients need to be randomized.

### Recruitment {15}

A total of approximately four contributing centers are planning to participate, which aim to include an average of 21 patients per year. The recruitment of all 168 patients should be completed within 24 months.

## Assignment of interventions: allocation

### Sequence generation {16a}

The patients will be assigned two code numbers: the number of the contributing center plus a patient identity number, continuously ascending, starting with 001.

After registration, patients will be randomized in a 1:1 ratio to receive either standard care supported by a reminder app (Arm A) or standard care (Arm B) for treatment of radiation-related skin toxicity.

A stratified block randomization will be performed. Stratification will be done using the following prognostic factors:
Tumor site: oropharynx/oral cavity versus hypopharynx/larynx.Treatment approach: radio-chemotherapy versus radiotherapy alone.Participating site.

The randomization will be performed centrally at the ‘Zentrum für Klinische Studien’ (ZKS) at the University of Lübeck, Germany via fax. The proceeding is based on standard operating procedures (SOPs) of the ZKS. The fax document has to be completed and finally be signed and dated by the investigator. Once the randomization is allocated to the patient it cannot be changed.

### Concealment mechanism {16b}

Not applicable.

### Implementation {16c}

Generation of the allocation sequence, enrollment of participants and assignment of participants to interventions will be performed by specially trained physicians registered as investigators for this trial.

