## Assignment of interventions: blinding

### Who will be blinded {17a}

Data analysts and statisticians will be blinded.

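### Three sections of the protocol article contradict each other on who controls allocation, and concealment is wrongly entered as not applicable

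*Protocol article*

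**What the plan says.** Three consecutive items of the protocol article deal with allocation.

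- **Sequence generation {16a}.** After registration, "patients will be randomized in a 1:1 ratio". The method is given as "A stratified block randomization will be performed", with tumor site, treatment approach and participating site as factors. On location: "The randomization will be performed centrally at the" ZKS in Lübeck, by fax. On procedure: "The proceeding is based on standard operating procedures (SOPs) of the ZKS". On the investigator's part: "The fax document has to be completed and finally be signed and dated by the investigator". An allocation is final once it has been given.
- **Concealment mechanism {16b}.** The whole entry is "Not applicable".
- **Implementation {16c}.** One group is given all three tasks: "Generation of the allocation sequence, enrollment of participants and assignment of participants to interventions will be performed by specially trained physicians registered as investigators".

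Three other sections bear on the point. Who will take informed consent? {26a} gives consent to the same group of physicians that {16c} names. Who will be blinded {17a} says "Data analysts and statisticians will be blinded" and lists nobody else. Eligibility criteria {10} excludes patients in whom poor compliance is anticipated, which is a matter of judgement.

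**The concern.** Allocation concealment protects the decision to enrol: whoever makes it must not know which arm comes next. It is a separate safeguard from blinding, and an unblinded trial needs it just as much. Under {16c} as worded, the physicians who seek consent and enrol also produce the list and assign from it. Such a physician could decide, knowing the next arm, whether to approach a patient, whether to delay, or whether to apply the compliance exclusion.

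That exclusion matters here because the app is meant to work by improving adherence to skin and mouth care. If expected adherence influenced who entered which arm, the arms would differ on the factor the intervention is supposed to change. Adjustment for recorded covariates could not be relied on to remove the difference, because the judgement behind it need not be recorded.

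**Working it through.** **Side-by-side reading.** The plan gives no figure for this point, so the check is mainly a comparison of the text.

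| Step | {16a} | {16b} | {16c} |
|---|---|---|---|
| Generates the sequence | Not named; randomization is run at the ZKS under its SOPs | – | Investigators |
| Enrols | Investigator completes and signs the fax form | – | Investigators |
| Assigns the arm | ZKS, centrally, after registration | – | Investigators |
| Keeps the next arm hidden | Implied by registering before allocation | Declared not to apply | No safeguard; the generator is also the recruiter |

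1. On enrolment, {16a} and {16c} agree.
2. On assignment they conflict directly: the arm comes either from the central unit or from the investigators.
3. On generation, {16a} names nobody, but a list written by recruiting physicians would defeat the purpose of a central service. {16c} nevertheless says they write it.
4. {16b} is wrong under either account. If {16a} is right, the central fax service is the mechanism and should be described there. If {16c} is right, concealment still applies and is absent.

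**Two cases follow.**

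- *{16c} is followed.* Recruiters hold the list, so every upcoming assignment is knowable.
- *The ZKS generates and holds the list and releases the arm only after registration.* Allocation is concealed, and {16b} and {16c} are reporting errors.

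**Illustration of scale in the first case.** The documents supply 80 per arm, a two-sided 5% level, a chi-square test and a control rate of 85% (Sample size {14}). They supply nothing on steering, so the rest is assumed: the arms differ by a share *s* in their proportion of higher-risk patients, those patients have a risk 30 percentage points higher, and the app has no effect.

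Spurious difference = *s* × 30 points:

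- *s* = 10%: 0.10 × 30 = 3 points
- *s* = 20%: 0.20 × 30 = 6 points

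The exact rejection probability of the uncorrected chi-square test, summed over all pairs of binomial outcomes with 80 per arm, is:

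| True rates | Difference | Rejection rate |
|---|---|---|
| 85% vs 85% | 0 | 4.8% |
| 86.5% vs 83.5% | 3 points | 8.0% |
| 88% vs 82% | 6 points | about 18% |

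If 85% is taken as one arm's rate instead of the midpoint, the 3-point case stays at about 8% (85 vs 82, or 88 vs 85). The 6-point case runs from 16.5% (85 vs 79) to 21.1% (91 vs 85).

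**The case against.** The strongest reply is that {16a} already describes a working concealment procedure: register, allocate remotely under the unit's SOPs, then lock the result. On that view {16c} is a generic answer to a three-part checklist item, reusing the phrase given for consent. Investigators at four sites in two countries could hardly each generate a sequence that is also run centrally by fax.

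Much of this stands. The operational detail in {16a} makes it the more credible account, and most of the remedy is already in place. It remains an inference, however. {16a} never says who generates or holds the list, and the only sentence that does says the investigators. This is not detail left to a fuller document, because the article fills in both items and states them wrongly.

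A reader might also infer three stronger points that the text does not support:

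- **That allocation in this trial is in fact unconcealed or biased.** This follows only if {16c} is what sites do.
- **That enrolling physicians also grade the outcome.** The observers may be nurses, technicians or physicians, and nothing says that they recruit. Assessor blinding is in any case a different question.
- **That the block design makes assignments predictable.** The article gives no block size, it commonly would not, and withholding the size helps concealment.

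**Conclusion.** The contradiction is real and must be resolved before enrolment starts (planned for December 2019 under Trial status). {16a} and {16c} cannot both describe who assigns patients, and the entry under {16b} is wrong on either reading.

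The consequence is conditional. Selection bias is a risk if {16c} is followed as written. If the ZKS holds the list, the fault lies in the description alone. The article never calls the trial open-label. That patients and site staff know the arm is inferred, reasonably, from {17a} and from the nature of a reminder app on the patient's own phone.

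No stated sample size, power or error rate changes. The false-positive figures of about 8% and 18% show scale under an assumed 10% or 20% imbalance and a 30-point risk contrast. Neither assumption has a source in the document, and the finding does not depend on them.

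**What to change.** 1. **Implementation {16c}:** state that ZKS staff with no role in enrolment generate and hold the sequence, and that investigators only obtain consent, enrol and fax the registration form.
2. **Concealment mechanism {16b}:** replace the present entry with the central mechanism, in which the ZKS releases the arm only after the patient has been irrevocably registered.
3. **Check against practice:** confirm with the ZKS that its SOPs work this way before rewording, so that the text records what is done.

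The cost is a wording amendment, with ethics committee approval as the article requires for protocol changes. The fax service is already planned, and sample size, schedule and analysis stay as they are. If the check showed that investigators do hold the list, generation and custody would have to move to the ZKS before recruitment opens.
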